## Abstract

**Background:**

Like many low- and middle-income countries, almost half of the proportion of the South African population is under the age of 25. Given the peak age of onset for most mental health problems is in adolescence, it is vital that adolescents have access to mental health counselling. There are several initiatives to increase access to mental health counselling in South Africa, primarily through the integration of counselling for common mental disorders (CMD) into primary health care services, but adolescents (15–18 years of age) generally do not utilize these services. To address this gap, we will undertake a study to explore the feasibility of conducting a trial of the effectiveness of a community-based mental health counselling intervention for adolescents at-risk for a CMD.

**Methods:**

The study is a feasibility trial of the ASPIRE intervention, a four-session blended multi-component counselling intervention adapted for South African adolescents at risk for depression and alcohol use disorders. We will enrol 100 adolescents from community settings and randomly assign them to the ASPIRE intervention or a comparison condition. Feasibility measures, such as rates of recruitment, consent to participate in the trial and retention, will be calculated. Qualitative interviews with participants and counsellors will explore the acceptability of the intervention. The primary outcomes for a subsequent trial would be reductions in symptoms of depression and days of heavy drinking which will be measured at baseline, 6 weeks, and 3 months post-randomization.

**Discussion:**

This feasibility trial using a mixed-methods design will allow us to determine whether we can move forward to a larger effectiveness trial of the ASPIRE intervention.

**Trial registration:**

The trial is registered with the Pan African Clinical Trials Registry (PACTR20200352214510). Registered 28 February 2020—retrospectively registered, https://pactr.samrc.ac.za/TrialDisplay.aspx?TrialID=9795

## Background

Low- and middle-income countries (LMICs) are home to more than a billion adolescents, with a high proportion of adolescents and young people living in Africa [1]. Mental and substance use disorders are among the leading causes of years lived with disability (YLDs) among children and youth up to the age of 24 years globally, accounting for 25% of YLDs in this age group [2]. Early intervention for these disorders is critical given an individual’s health and behaviors in childhood and adolescence lay the foundation for health in later years, and impact on the health of their offspring [3]. Moreover, the well-being of adolescents is integrally linked to socio-economic development in LMICs [4], including South Africa.

Like many LMICs, there is a significant mental health treatment gap in South Africa. Approximately 30% and 17% of adults in South Africa meet diagnostic criteria for a lifetime and past year mental disorder respectively, yet less than a quarter ever receive treatment [5]. There have been several initiatives to increase access to mental health counselling in South Africa, primarily through the integration of community health worker-delivered counselling for common mental disorders (such as depression and alcohol use disorders) into primary health care (PHC) services [6–8]. While these efforts are starting to reduce the treatment gap for adults who access PHC services, adolescents rarely use health services offered on the primary care platform. Where youth-friendly clinics are available, these do not offer mental health counselling. Moreover, data suggests that at-risk adolescents globally and in South Africa under-utilize mental health services [9, 10] with only 30% of this at-risk population seeking help for mental health problems [11].

Failure to reach adolescents is a major service and treatment gap given this is the peak age of onset for most mental health problems. If left untreated, these problems predict adverse life trajectories [12]. Adolescents who do not seek or access mental health services run the risk of developing more advanced psychopathology in adulthood [13, 14] and are at greater risk for physical health comorbidities and injury [15]. For example, heavy alcohol use during adolescence may contribute to unsafe sex practices that increase the likelihood of unplanned pregnancies and sexually transmitted infections, such as HIV [16]. Addressing mental health problems at an early stage may also alleviate the long-term costs to society and the public health system of untreated mental disorders [17].

While there is some promising evidence for effective interventions to promote mental health among adolescents globally [18–22], available evidence from South Africa for the effectiveness of these interventions is primarily focussed on adults. There is evidence from South Africa to suggest that brief, structured counselling interventions, when task-shared to trained community health workers (CHWs), may improve mental health outcomes among adults [8]. Motivational interviewing (MI), behavioral activation, and problem-solving therapy (PST), are recommended interventions from the World Health Organization’s programme to reduce the mental health treatment gap [23]. In South Africa, 3–4 sessions of counselling that included elements of these recommended interventions improved depression and alcohol outcomes among patients presenting to healthcare facilitates [8]. There is good evidence that combining MI and cognitive behavioral treatments (CBT) leads to improved outcomes for people with depression [24, 25], alcohol and other substance use disorders [8], as well as those with comorbid alcohol use disorders and depression [26]. Despite both MI and CBT approaches (such as PST and behavioral activation) being used to intervene with adolescents in high-income countries [21, 27, 28], this blended multi-component counselling intervention had not yet been tested among this population in South Africa.

This paper describes the study protocol for a feasibility trial of the ASPIRE intervention, a multi-component counselling intervention for South African adolescents at risk for a common mental disorder (specifically depression and alcohol use disorders). This feasibility trial aims to provide the early evidence needed to help service planners develop and implement adolescent-oriented counselling. It is hoped that the findings from this feasibility trial will lay the groundwork for a future effectiveness trial of the ASPIRE intervention.

### Feasibility trial objectives

In this feasibility trial, standard trial procedures will be implemented to obtain information on the acceptability and feasibility of the ASPIRE intervention for South African adolescents, including safety considerations. We will also assess the feasibility of our study methods and counselling, training and supervision model that has been adapted for this population [29]. Using a mixed-methods design with qualitative and quantitative approaches, this feasibility trial will allow us to identify and refine issues pertaining to recruitment, retention, intervention delivery, data collection, randomization, and blinding prior to a future effectiveness trial.

The primary objectives are to (i) test the feasibility and acceptability of the ASPIRE intervention as well as (ii) the feasibility of all study procedures and performance of outcome measures to inform a fully powered future trial. A second objective is to explore the initial effect of this intervention on days of heavy drinking and symptoms of depression.

## Methods

This protocol is reported in accordance with the guidelines presented in the Standard Protocol Items: Recommendations for Interventional Trials (SPIRIT) checklist [30] and the Template Intervention Description and Replication guidelines [31].

### Trial design

An individually randomized two-arm feasibility trial, with embedded qualitative interviews will be conducted (see Consort diagram in Fig. 1). We will enrol 100 adolescents from community settings and randomly assign them to the ASPIRE intervention or a comparison condition. Participants will be tracked for 6-week and 3-month post-randomization follow-up assessments.

**Fig. 1 Fig1:**
[figure not shown]
Consort diagram of the study design

### Study setting

We will recruit participants from a mix of communities in and around Cape Town within the Western Cape (WC) province of SA. These communities are characterized by high levels of unemployment (> 70%) and CMDs among young people [32]. Study activities will take place at the South African Medical Research Council’s clinical research site in Delft, which is within easy access of several of these communities and at community-based organizations that provide services for at-risk adolescents and their families.

### Participants

To be eligible for inclusion in this study, participants must (1) be aged between 15 and 18 years old; (2) provide written informed assent/consent to participate in the study; (3) have written informed parental consent to participate if younger than 18 years of age; (4) screen at risk for depression with a score ≥ 10 on the Center for Epidemiology Studies Depression Scale short form (CES-D-10 [33];) and/or screen at moderate or severe risk for alcohol-related health problems, with a score ≥ 5 on the Alcohol, Smoking and Substance Use Involvement Test-Youth (ASSIST-Y [34]); and report at least 2 episodes of heavy drinking (≥ 5 standard drinks on a single occasion) in the last month. Participants will be excluded if they are currently receiving any form of treatment for a mental or substance use disorder.

### Participant recruitment and study procedures

We will use established community-based outreach techniques in organizations and places that adolescents frequent to identify potential participants. These methods were used successfully in previous studies to recruit larger samples of vulnerable populations, including youth [35]. While all contact with adolescents - including assessments and counselling sessions - has been planned as occurring face-to-face, the team may conduct telephonic recruitment, assessments or counselling sessions where necessary.  Fieldworkers will approach potential participants in various community settings. After explaining the purpose of the study, the fieldworker will request verbal consent to screen the adolescent for possible study inclusion. If the adolescent is not eligible, they will be thanked for their time and given health information materials. If they are eligible, but do not provide consent, reasons for lack of interest will be recorded. Where parental consent is not required, an appointment will be made for a study enrolment visit with eligible and interested adolescents. If parental consent is required, the fieldworker will contact the parent to obtain this prior to making an appointment for an enrolment visit. The fieldworker will follow a script for this discussion with the adolescent’s parent and will not disclose the mental health criteria on which their child was eligible. If the parent refuses to consent, the adolescent will not be enrolled.

At the enrolment visit that will take place at the South African Medical Research Council’s (SAMRC) clinical research site in Delft, the fieldworker will re-screen the participant to confirm study eligibility prior to obtaining written informed consent/assent to participate in the trial. Thereafter the fieldworker will administer the baseline assessment in either English, Afrikaans, or isiXhosa, the three official languages of the Western Cape province. The assessment includes socio-demographic information as well as information on mental health and behavioral problems, family relationships; and social support. All participants will then be matched with a trained ASPIRE counsellor to receive a counselling session. After counselling is completed, the trial manager will assign the participants to the intervention or comparison group. The counselling session will take place the same day as enrolment. A further three counselling appointments will be scheduled for adolescents allocated to the intervention group. These will be spaced at least a week apart from each other. Participants will have six weeks from enrolment to complete all four sessions, whereafter a participant will time out of the intervention. Irrespective of study arm, all participants will be asked to return for follow-up assessments at 6-week and 3-month post-enrolment. During these follow-up visits, a fieldworker will re-administer the baseline assessments. Participants will have 30 days from their scheduled appointment to complete these follow-up assessments before timing out of that appointment.

A random sample of approximately 30 adolescents who received the ASPIRE intervention will be recruited to participate in qualitative interviews to explore their perceptions of (1) intervention acceptability and suggestions for modification; (2) feasibility of study procedures; and (3) barriers and facilitators to participation and retention in counselling. These will take place after their final follow-up assessment. Counsellors delivering the intervention will also be interviewed to examine their experience of delivering the intervention and to identify any barriers and facilitators to intervention delivery. Transport or costs associated with transport required to attend study or counselling appointments will be provided or reimbursed. Participants will receive grocery vouchers for completing the baseline and follow-up assessments.

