**Fig. 3 Fig3:**
[figure not shown]
Standard Protocol Items: Recommendations for Clinical Trials (SPIRIT) Figure–schedule of data collection

**Table 2 Tab2:** Overview of feasibility and acceptability outcomes and progression criteria

Outcome	Evaluation	Progression criteria to controlled trial^**a**^
**Feasibility of recruitment**	• Numbers screened, number of eligible participants, number invited to participate, consent rates (for parents and adolescents), refusal rates and reasons for refusal	• Enrolment of at least 5 participants per week
**Appropriateness of data collection processes and outcome measures**	• Number of missing items and follow-up rates	• Less than 15% missing items for each measure
**Retention in the ASPIRE intervention**	• Number of participants who completed at least three sessions	• At least 70% of participants complete the counselling programme
**Counsellor competencies in delivering the ASPIRE intervention**	• Scores on a counsellor competency checklist	• 75% competency
**Feasibility of randomization**	• Number of consent/assent • Number of refusals to be randomized	• At least 80% participation
**Feasibility of blinding**	• Field staff perceived contamination	• Very minimal perceived contamination (less than 5%)
**Presence of adverse events**	• Number of study-related adverse events reported	• Less than 10% of participants reporting severe adverse events related to the study
**Acceptability of the ASPIRE intervention**	• Qualitative interviews with participants and counsellors following the feasibility trial	• Not applicable
	• Scores on the Child Evaluation Inventory (CEI) used to assess participants’ satisfaction with the intervention and how it was delivered	• More than 80% of participants scored a total of 60 or more on the CEI
**Acceptability of the study design and procedures**	• Participants will be asked to rate the acceptability of the study procedures, including (i) screening, (ii) consent, (iii) assessment (length, type of questions, mode of administration), (iv) randomization, (v) referrals (and uptake of referrals), and (vi) tracking for follow-up assessments. They will rate these items on a 5-point scale (from 1 = not at all acceptable to 5 = very acceptable).	• More than 80% of participants score 3 or more for each rating

^a^If one or more criteria are not met revisions should be considered before proceeding to a definitive trial

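### Interviews on retention in counselling are held after the final follow-up in an unstratified random sample, so counselling non-completers are likely to be under-represented, though not excluded

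*Protocol article*

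**What the plan says.** The section on participant recruitment and study procedures sets the frame and size of the interview sample: "A random sample of approximately 30 adolescents who received the ASPIRE intervention". One of its three topics is "barriers and facilitators to participation and retention in counselling"; the others are the acceptability of the intervention and the feasibility of study procedures. The timing is fixed in the next sentence: "These will take place after their final follow-up assessment". Table 2 is consistent with this, listing "Qualitative interviews with participants and counsellors following the feasibility trial" as an evaluation of acceptability, with no progression threshold attached.

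The same section keeps everyone in follow-up, whatever happens in counselling: "Irrespective of study arm, all participants will be asked to return for follow-up assessments at 6-week and 3-month post-enrolment". Each follow-up visit stays open for 30 days after its scheduled date. Counsellors are interviewed too, about delivery and what helped or hindered it.

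Retention in counselling also has a quantitative criterion in Table 2: "At least 70% of participants complete the counselling programme". It is evaluated by the number who complete at least three sessions.

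**The concern.** A sample meant to explain why adolescents leave counselling should contain enough of those who left. Here the interview is placed after the last study assessment, so selection depends on staying in the study for 3 months. If adolescents who abandon counselling are also more likely to miss that assessment, the draw thins out the group with the most direct knowledge of the barriers.

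Feasibility and acceptability are the primary objective, and the article says that qualitative indicators will guide changes before a definitive trial. The 70% criterion can show that retention was poor, but not why. The article records reasons for refusing to take part, but describes no collection of reasons for leaving after enrolment that would make up for thin interview data. Its Discussion also expects that retention, both in the four sessions and through the study, may be difficult.

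**Working it through.** The plan gives no figure for the make-up of the interview sample, so there is none to reproduce. The size of the effect can only be illustrated.

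**Inputs from the article**
- ASPIRE arm: 50 (Sample size considerations).
- Interviews: about 30.
- Completion at the retention threshold: 70% (Table 2), so completers = 0.70 × 50 = 35 and non-completers = 15.
- Attrition allowance: not stated. Going from 70 measured to 100 recruited implies 1 − 70/100 = 30%. This is back-solved, not a stated rate.
- Follow-up in the team's other studies: more than 80% (Discussion).

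**Assumption:** how many non-completers are lost before the 3-month assessment. The article does not say.

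**Formula:** expected non-completers among 30 interviews = 30 × (non-completers reaching the final follow-up) / (all in the arm reaching it).

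**Losses confined to non-completers**

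| Lost before 3 months | Frame | Non-completers in frame | Expected among 30 | Change from 9 |
|---|---|---|---|---|
| Draw from the whole arm | 50 | 15 | 30 × 15/50 = 9.0 | – |
| 5 | 45 | 10 | 30 × 10/45 = 6.7 | −26% |
| 10 | 40 | 5 | 30 × 5/40 = 3.75 | −58% |

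Losing 5 or 10 of 50 is 10% or 20% overall, inside the implied 30% allowance.

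**Losses shared between completers and non-completers.** At 80% overall follow-up the frame is 40.

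| Non-completers followed up | Non-completers in frame | Expected among 30 |
|---|---|---|
| 80% (same as overall) | 12 | 9.0 |
| 70% | 10.5 | 7.9 |
| 60% | 9 | 6.8 |
| 50% | 7.5 | 5.6 |
| 40% | 6 | 4.5 |

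At 70% overall follow-up the frame is 35. The expected number runs from 9.0 (70% of non-completers followed) down to 30 × 4.5/35 = 3.9 (30% followed). It falls below 9 only when non-completers are followed up less well than completers.

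**The undefined word *received*.** Allocation follows session 1, so everyone in the arm has had at least that session. If the word covers all of them, the figures above apply. If it meant completed, no non-completer could be drawn, and the frame would be 35 × 0.70 = 24.5 to 35 × 0.80 = 28 at 70% to 80% follow-up, short of the planned 30.

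**The case against.** The strongest reply is that leaving counselling is not leaving the study. Every participant is asked back at 6 weeks and 3 months, with transport covered, vouchers given and telephone assessment possible. A non-completer who attends at 3 months is in the frame. This stands. A reader might infer that the interviews will hear only from those who stayed; the documents do not support that, and even the less favourable scenarios above leave about 4 non-completers among 30.

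A reader might also blame the restriction to ASPIRE recipients. That is not the problem. The comparison arm has only session 1, given before allocation, so it has no further counselling to be retained in.

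The late timing has a plausible purpose. A detailed interview about the intervention before the last assessment could affect self-reported outcomes or reveal the arm to assessors who should be blinded. That is a good reason not to interview before the assessment is done or its window has closed. It is not a reason to leave out those who never attend. The article does not say in terms that attendance at 3 months is a condition of selection, but timing the interview after that assessment gives no interview point to someone who never has it.

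Random selection is a legitimate choice that keeps staff from picking interviewees, and it can be kept within strata. Completers can describe barriers as well. Other evidence exists: the 70% criterion, the satisfaction scores, the ratings of study procedures and the counsellor interviews. None of these gives a departed adolescent's own reasons. The full protocol may hold more detail on sampling and tracing, but it would have to depart from the timing sentence to reach those who were lost.

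**Conclusion.** The concern holds in a limited form. The interview timing, with an unstratified draw from a loosely defined group, gives no interview point to adolescents lost before the 3-month assessment. It is therefore likely to under-represent counselling non-completers on the topic they know best.

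Under the assumed losses of 5 or 10 non-completers, the expected number among 30 interviews is 26% to 58% lower than a draw from the whole arm would give. The loss would be nil if leaving counselling is unrelated to missing follow-up. No figure in the article fixes which case applies, so the range is an illustration and not an estimate. The quantitative retention criterion and the clinical outcomes are unaffected. This is a cheap improvement to one component of the primary objective, not a flaw that undermines the trial.

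**What to change.** 1. Define the interview frame as all adolescents allocated to ASPIRE, in place of those who received it.
2. Keep about 30 interviews, but stratify by sessions attended and select at random within strata. Aim for about 10 with fewer than three sessions, or take all of them if fewer exist. The fallback is needed because 50 × (1 − 0.80) = 10: an arm of 50 holds 10 non-completers only if completion is 80% or lower.
3. Invite non-completers whether or not they attend at 3 months. Interview them after that assessment, or once its 30-day window has closed if they do not attend. Allow the telephone, which the article already permits for recruitment, assessments and counselling. Outcome data and assessor blinding are then untouched.

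The cost is some tracing effort. No extra interviews are needed, but the sample is no longer a simple random one, so the report should state how many were invited and interviewed in each stratum. The change was still practical at the COVID-19 pause described under Trial status: 67 of 100 were recruited, 48 participants still needed a 3-month assessment, and procedures for resuming were being written.
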